## Abstract

Promoting subjective well-being is a crucial challenge in aging societies. In 2022, we launched a community-based intervention trial (the Chofu-Digital-Choju Movement). This initiative centered on fostering in-person and online social connections to enhance the subjective well-being of older adults. This paper describes the study design and baseline survey. This quasi-experimental study involved community-dwelling older adults aged 65–84 years in Chofu City, Tokyo, Japan. A self-administered questionnaire was distributed to 3742 residents (1681 men and 2061 women), and a baseline survey was conducted in January 2022. We assessed subjective well-being (primary outcome); psychosocial, physical, and dietary factors; and the use of information and communication technology variables (secondary outcomes) among the participants. After the intervention involving online classes, community hubs, and community events, a 2-year follow-up survey will be conducted to evaluate the effects of the intervention, comparing the intervention group (participants) with the control group (non-participants). We received 2503 questionnaires (66.9% response rate); of these, the analysis included 2343 questionnaires (62.6% valid response rate; mean age, 74.4 (standard deviation, 5.4) years; 43.7% male). The mean subjective well-being score was 7.2 (standard deviation, 1.9). This study will contribute to the development of a prototype subjective well-being strategy for older adults.

## 1. Introduction

Japan’s demographic landscape has shown notable progression toward an aging society, with the proportion of the population aged ≥65 years estimated to reach 30% by 2025 [1]. Aging is associated with worsening self-rated health status [2], cognitive impairment [3], and various life events such as bereavement [4,5]. Within this context, subjective well-being is a crucial factor in aging. Well-being is defined as the state where individuals realize their abilities, cope with the normal stresses of life, function productively, contribute to their community, and find contentment [6]. Notably, older adults with high levels of subjective well-being tend to exhibit lower risks of frailty and mortality [7,8,9]. Therefore, it has become imperative to maintain and improve the subjective well-being of older adults in aging societies, aiming to extend their healthy lifespans and overall life expectancy.

Social networks are the determinants of higher subjective well-being. Frequent contact with friends, emotionally positive exchanges, enjoyment, and shared good experiences can contribute to an individual’s subjective well-being [10]. Moreover, psychological intervention programs involving social interactions positively affect subjective well-being [11]. There are four key strategies identified by Suragarn et al. for enhancing social connections among older adults: (1) multi-generational programs, (2) aging-friendly communities, (3) group-based physical activity approaches, and (4) the use of information and communication technology (ICT) [12]. Of these, ICT use warrants particular attention because of its indirect influence on well-being by enhancing social capital [13], which is a feature of social organizations such as networks, norms, and social trust that facilitate coordination and cooperation for mutual benefit [14].

While prior community-based interventions aimed at improving the subjective well-being of older adults have been implemented [15,16,17], none have been community-based with ICT use, to the best of our knowledge. In this context, this study aims to assess the effect of a community-based intervention on improving subjective well-being among the older Japanese population. Accordingly, we launched a study project in 2022 and implemented a multi-component intervention based on strategies to create both in-person and online social connections.

In this study, we describe the study design and baseline characteristics of the participants of the intervention launched in 2022.

## 2. Materials and Method

### 2.1. Study Design, Study Setting, and Participants

The Chofu-Digital-Choju (CDC; Choju means longevity in Japanese) movement is a quasi-experimental study [18] spanning from January 2022 to March 2024, conducted in collaboration with industry, academia, and the government. The CDC movement aims to foster in-person and online social connections to enhance the subjective well-being of older adults. In January 2022, a survey was conducted by mailing a self-administered questionnaire to collect baseline data for the intervention study. A subsequent follow-up survey, following up on the baseline measurements, is scheduled for a 2-year period.

The study population comprises community-dwelling individuals aged 65–84 years as of 1 October 2022, living independently in two districts of Chofu City, Tokyo, Japan. Individuals older than 85 years were excluded since the response rate that can be employed was extremely low, according to a previous study [19]. These districts were selected through consultation with city and social welfare council employees based on previous surveys and demographic trends. Chofu City, located in the middle of Tokyo (Figure 1), had a population of 238,311 (115,964 men and 122,347 women) as of 1 October 2021, with 51,536 individuals (22,018 men and 29,518 women) aged ≥65 years, constituting 21.6% of older adults [20]. These districts are located in the south and north of the city, where more than half the households reside in apartment buildings and detached houses, respectively [21].

The sample size was determined through several steps, as follows: first, a previous review by Bolier et al. indicated that positive psychology interventions showed an effect size of 0.34 for subjective well-being [22]. To detect this effect using a *t*-test, 137 individuals were required in both the intervention and control groups (with a statistical power of 0.8 and a risk level of 0.05). Second, based on a previous survey [23], we estimated a dropout rate of approximately 20% over 2 years. Third, the expected valid response rate at baseline and follow-up was approximately 80%, based on previous baseline surveys [19,24]. The percentage of participants required in the intervention group was approximately 10% of the total participants. From these estimates, we calculated a baseline survey sample size of 2675 participants.

Figure 2 illustrates the study flow diagram. The intervention group consists of participants who received the CDC movement’s intervention, while the control group consists of those who did not. During the 2-year follow-up survey, we will ask the participants whether they engaged in any or all of the interventions, including attending online classes, visiting local community interaction hubs, and joining the community events organized by us. Subsequently, the participants who received at least one of these interventions will be categorized into the intervention group in accordance with the responses in the 2-year follow-up survey.

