### 2.2. Baseline and Follow-Up Surveys

As shown in Table 1, the key measurements included subjective well-being as the primary outcome and psychosocial function, physical activity and function, use of ICT, and dietary habits as the secondary outcomes. As additional measures, demographics, socio-economic status, and medical and lifestyle profiles were collected. The self-administered questionnaire, mirroring the items from the baseline survey, will be distributed to the participants, except those who died or relocated from the study area, during the 2-year follow-up survey.

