### 2.7. Statistical Analyses

All data in the baseline survey are presented as means (standard deviations) or proportions, considering sex differences. The main measures were compared between sexes using the chi-square test for nominal variables and Welch’s *t*-test for continuous variables. A significance level of α = 0.05 indicated statistical significance, and all statistical analyses were performed using IBM SPSS Statistics for Windows, version 29.0 (IBM Corp., Armonk, NY, USA).

As a primary analysis, repeated measures analysis of variance (ANOVA) will be used to verify the interaction between time (pre- and post-intervention) and group (intervention and control groups) to clarify the effect of the interventions on the subjective well-being of older adults after the follow-up survey. In cases where the interaction is significant, a multiple comparison test will be performed using the Bonferroni method. Before ANOVA is performed, propensity score matching with a ratio of 1:1 will be applied using logistic regression based on the baseline survey to reduce bias in background factors between the intervention (participants) and control (non-participants) groups.

A secondary subgroup analysis will be performed to detect differences in the effects of the types of interventions or the intervention frequency on subjective well-being.

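### Any participation over two years defines the groups, but matching uses only January 2022 data, so health or life events before a resident would have attended stay unbalanced and can bias the primary result.

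*Protocol article*

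**What the plan says.** Section 2.1 of the protocol article fixes group membership at the end of the study: "the participants who received at least one of these interventions will be categorized into the intervention group", according to the answers in the 2-year follow-up survey. The Figure 2 caption repeats this. Neither gives a participation window or an index date.

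Sections 2.5 and 2.1 spread the chances to take part over the period: 25 sets of six-week online classes, a hub open three times a week, and events about four times a month, within a study running from January 2022 to March 2024.

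For balance between the groups, section 2.7 states that "propensity score matching with a ratio of 1:1 will be applied using logistic regression based on the baseline survey". That survey was taken in January 2022. The primary analysis is then the time-by-group interaction in a repeated-measures ANOVA.

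The Introduction links ageing to worsening self-rated health, cognitive impairment "and various life events such as bereavement". On follow-up data, section 2.2 says: "The self-administered questionnaire, mirroring the items from the baseline survey, will be distributed to the participants", apart from those who have died or moved away. The baseline items in Table 1 include no dated life event.

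**The concern.** Take two residents aged 75 with the same January 2022 profile. One is admitted to hospital in month 4, never attends, and reports a low score at two years. The other stays well and first attends in month 10. The first is a control and the second is an intervention participant, and a propensity score built on January 2022 data treats them as a well-matched pair. The interaction then credits the intervention with a difference that arose before the second resident had attended anything.

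This is separate from the recall bias listed in the Discussion. Perfect attendance records would not remove it, because what happens after baseline helps to decide who attends. The limitations mention the quasi-experimental design and contamination, but not this mechanism. Nor is it a detail left to an analysis plan: the article itself sets both the exposure rule and the time at which the matching data were measured.

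**Working it through.** **The plan's own figures.** Section 2.1 takes it that "positive psychology interventions showed an effect size of 0.34 for subjective well-being", "with a statistical power of 0.8 and a risk level of 0.05", and concludes that "137 individuals were required in both the intervention and control groups". A two-sided two-sample t-test with d = 0.34 gives n = 136.8, so 137 per group, with power 0.80. The article adds "we estimated a dropout rate of approximately 20% over 2 years", 80% valid response at each survey and about 10% participation: 137 / (0.8 × 0.8 × 0.8 × 0.10) = 2675.8, stated as 2675. Both figures reproduce and neither is affected by this point.

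**Inputs from the article.** Participation 10% (a planning figure), SD 1.9 points (Table 2), 137 per group, target 0.34 SD.

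**Inputs that are assumptions.** Share q with a major event in two years: 10–20%. Score drop D still present at follow-up: 1–1.9 points. Attendance after the event relative to normal, r: one quarter to one half. The true effect is zero.

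**Bias.** With s_C and s_I the shares of affected residents among controls and participants, bias = D × (s_C − s_I), divided by 1.9 for SD units.

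**False-positive rate.** Two-sided normal test with SE = √(2/137) = 0.121 SD. This takes the SD of change as equal to the SD of the score (pre-post correlation 0.5).

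**Case A: every event precedes any chance to attend.** Attendance among the unaffected is x = 0.10 / (1 − q + qr). Then s_I = qrx / 0.10 and s_C = q(1 − rx) / 0.90. Central values q = 0.15, D = 1.5, r = 0.5:
- x = 0.10 / 0.925 = 0.1081
- s_I = 0.081 and s_C = 0.158
- bias = 0.0766 × 1.5 = 0.115 points = 0.060 SD, or 18% of 0.34

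**Case B: events uniform over 24 months.** Take time as a fraction of 24 months. Attendance has a constant rate h before the event and rh after it. Affected residents attend with probability a = 1 − ∫₀¹ exp(−ht − rh(1 − t)) dt, unaffected with n = 1 − exp(−h), and h is solved so that qa + (1 − q)n = 0.10. Same central values:
- h = 0.1095, a = 0.0788, n = 0.1037
- s_I = 0.15 × 0.0788 / 0.10 = 0.118 and s_C = 0.15 × 0.9212 / 0.90 = 0.154
- bias = 0.0354 × 1.5 = 0.053 points = 0.028 SD, or 8% of 0.34

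| q, D, r | Case A: bias (false-positive rate) | Case B: bias (false-positive rate) |
|---|---|---|
| 10%, 1.0, 0.5 | 0.028 SD (5.6%) | 0.013 SD (5.1%) |
| 15%, 1.5, 0.5 | 0.060 SD (7.9%) | 0.028 SD (5.6%) |
| 20%, 1.9, 0.25 | 0.157 SD (25.5%) | 0.070 SD (8.9%) |
| 15%, 1.5, 1 (attendance unchanged) | 0 (5.0%) | 0 (5.0%) |
| 15%, 1.5, 2 (attendance doubled) | −0.097 SD (12.7%) | −0.048 SD (6.8%) |

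Case B is closer to the article's staggered schedule. It roughly halves the bias, because many residents attend before their event and carry the low score into the intervention group.

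**The case against.** **Direction.** A reader might infer that the result is bound to be biased in favour of the intervention. The documents do not support that. Section 2.5 describes a hub built on emotional support from volunteers and classes joined from home, so bereaved or less mobile residents might attend more. The last row of the table shows the sign reversing. In part this cuts both ways: if most events halve attendance and the rest double it, with equal score drops, one third of events would have to be of the doubling kind to cancel the bias (2/3 × 0.5 + 1/3 × 2 = 1). A net bias in favour is therefore the likelier direction, but it is not established.

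**Size.** The larger figures need every event to come before any chance to attend, which the staggered schedule contradicts. Those who died or moved get no follow-up form, and non-response among the worst affected shrinks the bias further. In one simulated scenario (30% affected, attendance 0.3 of normal, drop of 1 SD), it fell from 0.086 to 0.058 SD when response among affected residents fell from 0.64 to 0.35. Recovery before the 2-year survey would also reduce it. These points stand.

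**Visibility.** A reader might also infer that the problem cannot be seen afterwards. That is too strong. Repeated Table 1 items such as cohabiters, frailty and activities of daily living show change between surveys, and the full follow-up form is not shown. But the change is undated, and frailty and daily activities are secondary outcomes that the intervention may itself alter, so their follow-up values cannot serve as adjusters.

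**Conclusion.** The design weakness holds; its size and direction are uncertain. An exposure rule covering the whole two years, paired with matching on January 2022 data alone, leaves events before a resident's likely attendance unbalanced. On the assumed inputs, the bias is about 0.01–0.07 SD (4–21% of the planned effect), with a false-positive rate of about 5–9% rather than 5%. It reaches 0.03–0.16 SD and 6–26% only if all events precede any opportunity. The sign probably favours the intervention where events keep people away and reverses where they bring people in. At the central values this bias would seldom produce a positive result by itself, but the data as described give no way to tell how much of an observed interaction it explains.

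**What to change.** **Follow-up form.** Add the month and year of first participation, checked against class, hub and event records where these are held. Add yes/no with month and year for bereavement, hospitalisation, new need for long-term care, and starting to care for a family member.

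**Companion analysis, prespecified beside the planned one.** Give each matched control the participant's first-participation date as index date. Match on events between baseline and that date, or exclude pairs with one. Leave later events in, since the intervention may affect them. Preferably draw controls from those not yet participating at the index date.

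**Expected gain.** On the Case B inputs with exact dates, excluding earlier events leaves 0.003 SD or less when controls are residents who never attend, and removes this bias when they are residents not yet participating. In the latter choice about 5–6% of controls would go on to attend, which slightly dilutes a true effect.

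**Limitations section.** State that a bias of uncertain direction remains.

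**Cost.** A few extra questions on a form that the article describes as still to be sent. Some pairs are lost, but most can be replaced because non-participants outnumber participants by about nine to one at the planned 10%. Dates recalled to the month over two years will contain error, which is why this suits a companion analysis rather than a replacement for the primary one.

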### 2.2. Baseline and Follow-Up Surveys

As shown in Table 1, the key measurements included subjective well-being as the primary outcome and psychosocial function, physical activity and function, use of ICT, and dietary habits as the secondary outcomes. As additional measures, demographics, socio-economic status, and medical and lifestyle profiles were collected. The self-administered questionnaire, mirroring the items from the baseline survey, will be distributed to the participants, except those who died or relocated from the study area, during the 2-year follow-up survey.

### 2.3. Primary Outcome Measures

Subjective well-being was assessed using the Cantril Ladder, which evaluates people’s attitudes toward their lives and components in various respects [25]. The scale comprised an 11-level Likert scale ranging from 0 (lowest) to 10 (highest).

### 2.4. Secondary Outcome Measures

#### 2.4.1. Psychosocial Function

Social isolation was assessed according to the frequency of outings or contact with family members, relatives, and friends. Social isolation was defined as contact with others less than once a week [26]. Neighborhood relationships were assessed using a four-point scale encompassing “visiting each other”, “standing and chatting”, “exchanging of greetings”, or “none [27,28]”. Additionally, social participation was evaluated based on the frequency of participation in the following activities or groups more than once a month: volunteering, civic action, and nonprofit organizations; sports groups; hobbies and learning groups; senior citizen clubs; neighborhood associations; and others [23].

Psychological aspects include health literacy [29], psychological health [30,31], and depressive mood [32,33].

#### 2.4.2. Physical Activity and Physical Function

Exercise habits were defined as engaging in any exercise one or more times a week and recreational walking or walking for transport for 150 min or more a week [34,35]. Physical function was evaluated according to frailty status [36,37], activities of daily living [38], and the Motor Fitness Scale [39].

#### 2.4.3. Dietary Habits

Dietary variety and food frequency scores were used to evaluate dietary variety [40,41]. The participants were also asked about their status of eating alone [42].

#### 2.4.4. Use of ICT

The questionnaire assessed the type of ICT device used weekly or more frequently and the frequency of Internet usage, such as browsing web pages and exchanging e-mails [43,44].

### 2.5. Intervention Overview

The CDC movement aims to improve the subjective well-being of older adults by creating in-person and online connections. After completing the baseline survey, we will implement the community-based intervention designed by the CDC movement. This intervention consists of online classes, community hubs, and community events.

The online classes integrate an intervention approach combining exercises, nutrition, and cognitive aspects effective in preventing frailty [45]. Additionally, this class employs the Coimagination Method to foster formal conversation techniques aimed at building relationships [46,47]. The exercise component involves workouts designed by professional instructors based on the 10-item muscle training validated in the Japanese Oniishi Model [48,49]. The Oniishi Model’s muscle training is derived from the 19-item regimen by Fiatarone et al. [50] and focuses on fundamental movements such as walking and standing. For safety in an online environment, no specific intensity is designated for the training. The nutrition component, supervised by nutrition experts, includes lectures on diet and food intake for frailty prevention [40]. The lectures center around a mnemonic phrase in Japanese, “sa-a-ni-gi-ya-ka-ni-i-ta-daku” (‘Let’s eat with diversity’), highlighting the importance and techniques of consuming a variety of food groups for frailty prevention [23]. The cognitive aspect involves cognitive enhancement activities led by trainers, such as finger exercises and short-term memory stimulation. The Coimagination Method, designed for equitable participation in communication, comprises two phases, as follows: participants explain their pre-prepared photos and answer questions from others. This process is repeated until all participants have completed both phases. Each session of the online classes focuses on themes such as landscapes, favorite foods, passions, health, and memorable experiences, with facilitation to encourage conversation. Each group, consisting of about ten members, meets once a week for six weeks. The weekly online classes include exercises, nutrition, cognitive aspects, and the Coimagination Method, with participants joining from their homes. Throughout the intervention period, a total of 25 sets of these online classes will be conducted with different participants.

The community hub, serving as a local third place, is operated with the intent of promoting well-being through emotional support provided by volunteers [51,52]. This social interaction center aims to foster trust by listening to and empathizing with the elderly residents of the area. Additionally, it seeks to facilitate social support for older individuals through collaboration with external agencies when necessary [53]. To motivate visits to the hub, health measuring devices are installed, and consultations on smartphone usage are offered. The health measuring devices are capable of assessing or estimating blood pressure, vegetable intake, hemoglobin levels, autonomic nerve function, balance, and cognitive abilities. The hub is open three times a week during the intervention period, with volunteers present during operating hours.

As community events, activities ranging in size from a few to about 30 participants are conducted, being open to all age groups, from youth to the elderly. The themes of these events include general health, exercise, diet, hobbies and entertainment, and the use of ICT such as smartphones. These events are held about four times a month in community centers or university facilities.

